**Background**

An individual’s maximum height attained during adulthood is both heritable and one that is heavily influenced by childhood environmental exposures (Silventoinen 2003) . Adverse circumstances during periods of rapid growth in childhood, such as low socioeconomic status, childhood illness, and nutritional deprivation, have been shown to be associated with decreased adult height attainment (Tucker-Seeley and Subramanian 2011),(Bozzoli, Deaton et al. 2009),(Steckel 1995). Adult height is also associated with future health and well-being. Studies have found that height is negatively associated with mortality from a variety of non-communicable diseases (Emerging Risk Factors Collaboration 2012) and declines in cognitive function (Case and Paxson 2008), and positively associated with future economic potential and earnings (Case and Paxson 2006).

Two recent studies have found that among low and middle income countries, countries in Africa have experienced significant declines in height across recent birth cohorts, while heights have generally increased in countries located in Europe, Eastern Mediterranean, South-East Asia and the Western Pacific (Akachi and Canning 2010),(Subramanian, Özaltin et al. 2011). Within countries, gains and losses in height are concentrated among socioeconomic groups. In a study examining height across birth cohorts in 54 low and middle income countries, declines in mean height across birth cohorts were found to be greater among the poorest wealth quintiles while gains in mean height were more pronounced among the wealthier quintiles (Subramanian, Özaltin et al. 2011). Such studies may point toward inequity in how changes in height attainment occur in populations over time.

The epidemiologist Geoffrey Rose argued that for most risk factors, such as blood pressure and cholesterol, as the average level in the population changed, the “dispersion around the average remains rather constant” (Rose, Khaw et al. 2008). While his findings suggested that this hypothesis also applied to BMI (Rose and Day 1990), studies have since found that weight gain tends to be concentrated among higher percentiles of the BMI distribution within a population (Razak, Corsi et al. 2013). Thus, a similar reliance on the mean as a summary measure of height may obscure significant changes in the distribution of height over time within and across populations that have important implications for health equity.

This study seeks to 1) describe changes in adult height across cohorts 2) assess whether changes in mean height are related to changes in the dispersion of height across birth cohorts within and across countries, 3) determine whether patterns exist with regard to which parts of the height distribution experience the greatest height gains or losses across birth cohorts.

**Methods**

**Data Sources**

Data for this analysis will obtained from the Demographic and Health Surveys (DHS), which are nationally representative, cross-sectional household surveys that have been conducted regularly in about 70 countries since 1984 (Rutstein 2006). DHS surveys are intended to be comparable over time and across countries. To achieve this, DHS employs standardized interviewer training, measurement tools, data collection techniques and questionnaires (ORC MACRO 2006). DHS ensures that they are nationally representative by employing a multistage stratified cluster design. Strata are defined by urban and urban locality, as well as by large administrative units, such as states or regions. During the first stage, the sampling frame is comprised by a complete list of primary sampling units (PSUs), developed based on unique geographic units (often census enumeration areas) that cover the entire country. PSUs are then selected within each stratum with probability proportional to size sampling (PPS) based on the number of units, meaning that each unit has a defined, equal probability of selection. Second, a listing of all households within a selected PSU is generated through field visits. From the list, a fixed sample of households is selected with equal systematic probability (ICF International 2012). The final sample size ranges from 5000 and 30 000 households, depending on the country (Corsi, Neuman et al. 2012).

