**Analysis**

We will use a pooled dataset that includes all countries and survey waves. We will also create a second database also that includes summary percentile values and 33-quantile values for the height distribution in each country for each birth cohort. Stata v14.0 (StataCorp 2015) will be used to conduct the statistical analysis and graphics will be produced using the statistical package R (R Core Team 2013).

Research Question 1 will be addressed as follows. Summary tables that describe basic statistics of the population will be constructed according to country and birth cohort. These tables will include change in mean height and standard deviation of height for each country. An F-test for equality of variance will be performed to test the difference in SD between the earliest and most recent birth cohorts for each country.

Research Questions 2 and 3 will be addressed using both graphical and statistical approaches.

Graphical Analyses

Graphical approaches will be used to examine height within countries across birth cohorts. The first type of plot created will be the Quantile-Quantile (QQ) plot, which has previously been used to examine distributional changes in BMI (Razak, Corsi et al. 2013). QQ plots are particularly effective at depicting change at the tails of the distribution (Wilk and Gnanadesikan 1968). To construct the QQ plot, 33-quantiles (1^st^, 4^th^…94^th^, 97^th^) of height (y-axis) from the most recent birth cohort were plotted against the corresponding 33-quantiles of height (x-axis) from the earliest birth cohort for each individual country. 33- quantiles were used instead of percentiles in order to improve the smoothness of the graphical distributions. If the distribution of height remains the same across birth cohorts, regardless of overall gains or decreases in height within the country, the QQ plot will fall on the line of equality (line y=x). If segments of the QQ plot fall above the line, it indicates that certain segments of the population experienced disproportionate gains in height, while if the plot falls below the line of equality, it indicates that segments of the population experienced declines in height across birth cohorts.

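### The SAP describes PPS selection as equal probability and specifies no sampling weights, strata or PSUs for any country-cohort summary or for the F-test

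*SAP*

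**What the plan says.** Under Data Sources the SAP rests representativeness on the sampling design: "DHS ensures that they are nationally representative by employing a multistage stratified cluster design". It then describes that design in three steps.

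- Stratification: "Strata are defined by urban and urban locality, as well as by large administrative units, such as states or regions" (the second locality is presumably rural). No allocation or sampling fraction per stratum is given.
- Stage one: the draw of PSUs in a stratum is described as "probability proportional to size sampling (PPS) based on the number of units, meaning that each unit has a defined, equal probability of selection".
- Stage two: "From the list, a fixed sample of households is selected with equal systematic probability".

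The Analysis section opens with "We will use a pooled dataset that includes all countries and survey waves" and adds a second database of "summary percentile values and 33-quantile values for the height distribution in each country for each birth cohort". From these come the tables of mean and SD, an F-test of the SD in the earliest against the most recent cohort in each country, the QQ and mean-difference plots, and the multilevel models. None of these steps mentions sampling weights, strata or PSUs. The SAP does not say that the samples are self-weighting.

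**The concern.** The first-stage sentence is the SAP's main statement about selection probability, and it says that the probability is equal. A programmer who takes it at its word has no reason to weight. Nothing later in the plan corrects this.

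If some strata are sampled more heavily than their population share, and women in those strata are taller or shorter, then unweighted means and tail percentiles describe the mix of the sample and not that of the country. These quantities feed all three research questions. If the departure from population shares also differs between waves, part of it can pass for a change between birth cohorts, which is what the study sets out to measure. The SAP's own Background says that height gains and losses are concentrated in socioeconomic groups, so composition cannot be assumed harmless.

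Separately, the plain F-test treats women as independent observations, although the SAP describes a clustered, stratified sample.

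**Working it through.** The SAP gives no figure to reproduce here. The first step is algebra on the stated design. All numerical inputs in steps 2 to 4 are assumptions, because the SAP gives no stratum sizes, allocations or height differences.

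**1. Selection probabilities.** Let m PSUs be drawn by PPS in stratum h, let M_hi be the number of households in PSU i, and let b be the fixed take per PSU.

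- P(PSU) = m × M_hi / ΣM_h
- P(household given PSU) = b / M_hi
- P(household) = m × b / ΣM_h

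PSU size cancels but stratum size does not.

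**2. Illustration.** Take PSUs of 100, 200, 300 and 400 households in equal numbers, with m = 20 and b = 25.

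- Stratum of 100 PSUs: ΣM = 25 × (100 + 200 + 300 + 400) = 25,000. PSU probabilities are 0.08, 0.16, 0.24 and 0.32. Household probability is 20 × 25 / 25,000 = 0.020 in every PSU.
- Stratum three times as large, same m and b: 500 / 75,000 = 0.00667.

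So PSU probabilities are unequal, household probabilities are equal within a stratum, and they differ threefold between these two strata. Even within a stratum, equality needs the field listing to match the frame size: a listing 30% larger multiplies the household probability by 1 / 1.3 = 0.77.

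**3. Bias of unweighted summaries.** With sample urban share w, population urban share W and urban-rural height difference d:

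bias in mean = (w − W) × d

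- 0.10 × 0.5 = 0.05 cm
- 0.15 × 1.5 = 0.225 cm
- 0.20 × 2 = 0.40 cm

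For the SD and tails, assume a two-component normal mixture with within-stratum SD 6 cm. At W = 0.30, w = 0.50, d = 2:

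- SD: √(0.25 × 4 + 36) − √(0.21 × 4 + 36) = 6.083 − 6.070 = 0.013 cm
- 5th percentile: +0.373 cm
- 95th percentile: +0.416 cm

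Over a wider set (W 25 to 30%, w 40 to 50%, d 1 to 3 cm) the bias is 0.10 to 0.75 cm in the mean, 0.10 to 0.65 cm in the 5th percentile, 0.10 to 0.81 cm in the 95th, and 0.002 to 0.046 cm in the SD. If w = W, all four are zero. If the urban share is too low, the sign reverses.

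**4. Passage into a cohort contrast.** If both cohorts carry the same (w − W) × d, the bias cancels in the difference. Whether it does depends on which waves supply each cohort. Women are eligible at ages 25 to 49 in waves from 1993 to 2013.

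- Born 1950-59: eligible until about 2008-09 (1959 + 49 = 2008).
- Born 1980-89: eligible from about 2005 (1980 + 25 = 2005).

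The windows overlap only from about 2005 to 2008. Even then a wave holds few of the relevant birth years: a 2005 wave spans births 1956 to 1980, so four years of the older decade and one of the younger. These two cohorts therefore come largely from different waves. Adjacent decades often share waves, and much of a common bias cancels.

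The full 0.05 to 0.40 cm becomes spurious cohort change only if one cohort's waves have the stated imbalance and the other's do not. There is also a smaller route with constant allocation. If w − W stays at 0.20 but d grows from 1 to 2 cm, the artefact is 0.20 × (2 − 1) = 0.20 cm.

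**The case against.** The best defence is that the selection sentence is loose and not wrong. It speaks of selection within each stratum and of a size measure based on the number of units, so the unit could be the household. Step 1 shows that households in one stratum then do have equal probability. This stands in part. But the preceding sentence of the SAP uses unit for the geographic PSU, the sentence credits the first stage with a property that needs both stages, and equality across strata or surveys does not follow.

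A reader might infer more than the SAP supports in four ways.

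- That the plan has chosen an unweighted analysis. It has not; it is silent on weights.
- That the sampling fractions do differ between strata and waves. The SAP gives none, so this is a possibility only.
- That the plan claims national figures which are then wrong. The SAP calls the surveys nationally representative; it does not use those words of its cohort summaries.
- That the SD is distorted as much as the mean. Step 3 shows that it is not, so the SD model and the SD comparison are little affected by this bias.

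Nor can the gap be left to a protocol: how an estimate is computed from a complex sample is a matter for the SAP.

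**Conclusion.** The point holds as a specification gap together with one incorrect sentence. It is a cheap improvement, not a demonstrated error in results.

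Followed as written, the plan yields unweighted country-cohort summaries. They are biased only if allocation is disproportionate and height differs between strata. Under the assumed range (0.5 to 2 cm, 10 to 20 points) the bias is 0.05 to 0.40 cm in the mean and about the same in the tails. It is very small in the SD and nil under proportional allocation. The SAP's content does not allow a narrower range.

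The bias reaches a cohort contrast so far as the cohorts come from waves with different allocations, or the stratum height difference itself changes. The contrast of 1950-59 with 1980-89 is the most exposed.

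The independence problem with the F-test is separate and does not depend on these figures.

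**What to change.** - Data Sources: reword the selection sentence. PSUs have probability proportional to size; with a fixed take, household probability is about equal within a stratum of one survey; it may differ across strata and surveys.
- Analysis: state that every country-cohort mean, SD, percentile and 33-quantile is computed with the survey sampling weights, and give one rule for rescaling the weights when waves of a country are pooled. One option is for each wave to contribute in proportion to its number of eligible women, saying whether that number is in the sample or in the population.
- Research Question 1: replace the plain F-test with a comparison of SDs whose variance accounts for strata and PSUs within each survey.
- Statistical Analyses: leave the multilevel model's structure as it is. Its observations are country-cohort summaries, so design-based variance does not carry over to it directly. It gains from weighted inputs.

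The cost is a few sentences in the SAP, use of the surveys' weight, stratum and PSU variables, a little more programming, and some loss of precision from variable weights.

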**Study Population and Sample Size**

The study population will include women aged 25-49 available from survey waves spanning from 1993 to 2013. Women aged less than 25 will be excluded from the sample in order to ensure that full height attainment had been achieved. Women with missing height values or with implausible values recorded for height (less than 100cm or greater than 200 cm) will also be excluded from the study (Subramanian, Özaltin et al. 2011).

**Outcome and Exposure**

Attained height (measured in centimeters) will be specified as a continuous variable, and is considered to be accurate to 1 millimeter (Macro International Inc. 2008). The standard deviation (SD) and the 5^th^ and 95^th^ percentiles will also be used as outcomes in statistical modeling because they provide information on how the distribution of height changes between and within countries over time.

The primary exposure of interest was considered to be cohort. To compare women over time, women will be divided into birth cohorts ranging from 1950-59, 1960-69, 1970-79, and 1980-89 within each country.

**Analysis**

We will use a pooled dataset that includes all countries and survey waves. We will also create a second database also that includes summary percentile values and 33-quantile values for the height distribution in each country for each birth cohort. Stata v14.0 (StataCorp 2015) will be used to conduct the statistical analysis and graphics will be produced using the statistical package R (R Core Team 2013).

Research Question 1 will be addressed as follows. Summary tables that describe basic statistics of the population will be constructed according to country and birth cohort. These tables will include change in mean height and standard deviation of height for each country. An F-test for equality of variance will be performed to test the difference in SD between the earliest and most recent birth cohorts for each country.

Research Questions 2 and 3 will be addressed using both graphical and statistical approaches.

Graphical Analyses

Graphical approaches will be used to examine height within countries across birth cohorts. The first type of plot created will be the Quantile-Quantile (QQ) plot, which has previously been used to examine distributional changes in BMI (Razak, Corsi et al. 2013). QQ plots are particularly effective at depicting change at the tails of the distribution (Wilk and Gnanadesikan 1968). To construct the QQ plot, 33-quantiles (1^st^, 4^th^…94^th^, 97^th^) of height (y-axis) from the most recent birth cohort were plotted against the corresponding 33-quantiles of height (x-axis) from the earliest birth cohort for each individual country. 33- quantiles were used instead of percentiles in order to improve the smoothness of the graphical distributions. If the distribution of height remains the same across birth cohorts, regardless of overall gains or decreases in height within the country, the QQ plot will fall on the line of equality (line y=x). If segments of the QQ plot fall above the line, it indicates that certain segments of the population experienced disproportionate gains in height, while if the plot falls below the line of equality, it indicates that segments of the population experienced declines in height across birth cohorts.

The second plot type that will be used is the mean-difference plot. Mean difference plots graph the differences between corresponding quantiles on the y-axis against the means of the same quantile on the x-axis. The point’s location on the y-axis shows the direction and magnitude of the shift in relation to its difference from the horizontal line representing zero (Flegal and Troiano 2000). Mean-difference plot will be created for each country showing the shift in distribution of height between the most recent birth cohort and the earliest birth cohort available for each country. Points that fall below the line at zero indicate losses in height at that place in the distribution, while points that fall above the line indicate gains in height.

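### The country-level F-test for equal variances assumes independent normal data, which this clustered survey with very wide height limits does not supply, so its p-values are unreliable and tend to be too small

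*SAP*

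**What the plan says.** - **The test.** Under Analysis (Research Question 1) the SAP plans summary tables by country and birth cohort, with the change in mean and SD. It adds: "An F-test for equality of variance will be performed to test the difference in SD between the earliest and most recent birth cohorts". It gives no significance level, sidedness, normality check or robust alternative.
- **The sampling.** Under Data Sources: "DHS ensures that they are nationally representative by employing a multistage stratified cluster design". Then: "PSUs are then selected within each stratum with probability proportional to size sampling (PPS) based on the number of units", and within each PSU: "From the list, a fixed sample of households is selected with equal systematic probability". The number of households per PSU is not given.
- **The height limits.** Under Study Population and Sample Size, women with "implausible values recorded for height (less than 100cm or greater than 200 cm) will also be excluded from the study". Every value between those limits stays in.
- **Measurement.** Outcome and Exposure takes height as accurate to 1 mm. No rate of gross recording error is given.
- **Nesting.** The multilevel models under Statistical Analyses place cohorts within countries and are fitted to country-cohort summaries. They do not represent women within PSUs and have no bearing on the F-test.

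**The concern.** The variance-ratio F-test is exact only for independent samples from normal distributions. Two features of the plan depart from that.

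- **Clustering.** Women in one PSU are not independent.
- **Tail weight.** For independent data the large-sample variance of log s² is (kurtosis - 1)/n. This equals the 2/n behind the F-test only when kurtosis is 3. A few extreme records raise kurtosis sharply, and a larger sample does not cure this.

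Change in dispersion is a central subject of the study, and this is the only formal country-level inference on change in SD that the SAP plans. The quantile plots carry no stated inference, and the multilevel models pool countries. If the p-values are too small, some countries will appear to show a changed spread of height when the data do not support it.

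**Working it through.** The SAP states no error rate or power for this test, so there is no figure to reproduce.

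**Inputs.** From the SAP: the test, the cluster design and the limits of 100 and 200 cm. Assumed: two-sided 5%, mean 155 cm, SD 6.5 cm, 1000 or 3000 women per country-cohort, 5 to 25 women per PSU and cohort, ICC 0.05 to 0.2, and the error shares and shapes below.

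**1. Baseline.** On independent normal data with equal variances (4000 simulated runs) the F-test rejects in 5.1% (n = 1000) and 5.4% (n = 3000). It behaves properly when its assumptions hold.

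**2. How far out the limits lie.** (155 - 100)/6.5 = 8.5 SD below the assumed mean and (200 - 155)/6.5 = 6.9 SD above it. They would remove very few gross errors.

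**3. Level under heavy tails.** With D = (kurtosis - 1)/2, the true level is 2 × [1 - Φ(1.96/√D)]. For a share e of records uniform on 100 to 200 cm, the deviation from 155 runs from -55 to 45. Its mean square is 25 + 10000/12 = 858.3, and its mean fourth power is (45⁵ + 55⁵)/500 = 1375625. For the normal part these are 6.5² = 42.25 and 3 × 6.5⁴ = 5355.2.

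For e = 0.5%:
- variance ≈ 0.995 × 42.25 + 0.005 × 858.3 = 46.33
- fourth moment ≈ 0.995 × 5355.2 + 0.005 × 1375625 = 12207, or about 12200 after centring on the mixture mean
- kurtosis = 12200/46.33² = 5.68, so D = 2.34
- level = 2 × [1 - Φ(1.96/1.53)] = 20%

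| Error shape | Share of records | Kurtosis | True level |
|---|---|---|---|
| Uniform on 100-200 cm | 0.1% | 3.63 | 8.7% |
| Uniform on 100-200 cm | 0.3% | 4.74 | 15.2% |
| Uniform on 100-200 cm | 0.5% | 5.68 | 20.0% |
| Error SD 20 cm | 0.1% to 2% | 3.14 to 5.13 | 5.8% to 17% |
| Misreads of 10 cm | 0.1% to 2% | 3.01 to 3.10 | 5.0% to 5.6% |

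Simulation agrees for the uniform shape: about 8% at a share of 0.1% and 19% to 20% at 0.5%, at both sample sizes.

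**4. Level under clustering alone.** With normal PSU effects and m women per PSU, D = 1 + (m - 1) × ICC². For m from 5 to 25:
- ICC 0.05: D = 1.010 to 1.060, level 5.1% to 5.7%
- ICC 0.1: D = 1.04 to 1.24, level 5.5% to 7.8%
- ICC 0.2: D = 1.16 to 1.96, level 6.9% to 16%

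The effect is small because the ICC enters squared. These figures treat the two cohorts as coming from different PSUs. If both come from one wave, shared PSU effects correlate the two variances positively and offset part of the excess.

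**5. Error rates that differ between cohorts.** With equal true SDs but uniform errors in 0.1% of one cohort and 0.5% of the other, the F-test rejects in 26% (n = 1000) and 51% (n = 3000) of runs. This is bias in the SD, not a matter of test level. It can arise because the pooled waves run from 1993 to 2013, so the two cohorts may come from different waves.

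**6. Is a robust test enough?** Brown-Forsythe restores the level to 4.1% to 5.6% with equal uniform error shares of 0.1% to 1%. With 10 women per PSU and ICC 0.2 it still rejects in 8.6% to 8.8%. With the unequal error rates of step 5 it rejects in 6.6% (n = 1000) and 10.8% (n = 3000).

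**The case against.** The strongest reply is that the effect may be negligible. The SAP gives no gross-error rate and treats height as accurate to 1 mm. The uniform error shape is close to a worst case, and misreads of 10 cm barely move the level. Clustering at an ICC of 0.05 adds less than one percentage point. The test accompanies a descriptive table with no stated decision rule, and Research Questions 2 and 3 do not use its p-values. All of this stands. It limits the size of the point but does not justify a test whose assumptions the SAP's own description of the data contradicts.

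Three stronger readings may tempt a reader, and the SAP does not support them.

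- **That unequal selection probabilities and weights inflate the error.** Data Sources says that the selection of PSUs gives each unit an equal chance, and the SAP specifies no weighting. Unequal weights inflate the variance of a weighted estimate, and the planned test is unweighted.
- **That a number of falsely flagged countries can be stated.** The figure of about 70 countries is the reach of the survey programme, not the number analysed here. Such a count would also assume that every null is true and that inflation is the same everywhere.
- **That clustering alone makes the test badly wrong, or that shared PSUs make it worse.** The first needs an ICC near 0.2 or large clusters. The second runs the other way.

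**Conclusion.** The point holds, and the SAP should be changed. The planned F-test does not suit data that the SAP itself describes as clustered, with limits that would let gross errors through. Its country-level p-values are unreliable and tend to be too small.

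The size is an assumption. At a nominal 5%, the true level is about 5% with misreads of 10 cm or an ICC of 0.05, and about 20% if 0.5% of records are spread evenly over 100 to 200 cm. Tail weight is potentially the larger cause; clustering is secondary unless the ICC is near 0.2 or clusters are large. That the method is unsuitable is clear from the text; where in this range the study falls is not. The country statements on change in SD are affected. The multilevel models do not use these p-values, but their SD outcomes would carry the bias shown in step 5 if error rates differ between cohorts.

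**What to change.** - Replace the F-test by the log ratio of SDs (most recent over earliest cohort), with a 95% confidence interval from a bootstrap or jackknife that resamples PSUs within strata within each survey. Where one survey feeds both cohorts, resample its PSUs once and recompute both SDs, so that the shared PSU effect is carried through.
- State whether the SDs are weighted. If they are, use the survey weights in every replicate.
- Report the change in the P95-P5 range beside the SD ratio, or repeat the comparison with tighter height limits fixed in advance. A better interval does not cure bias from differing error rates. The SAP already uses the 5th and 95th percentiles as outcomes. For a percentile range, prefer the bootstrap to a delete-one jackknife.
- Brown-Forsythe alone is not enough, for the reasons in step 6. False discovery rate control across countries is optional.

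The cost is SAP wording and computing time, with no new data. Some countries may lose nominal significance.

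### The QQ-plot reading rule is wrong as written: a uniform gain or loss d falls on y = x + d, not y = x, so a uniform gain would be read as disproportionate

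*SAP*

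**What the plan says.** The SAP, under Analysis (Graphical Analyses), builds one QQ plot per country from the 33-quantiles "of height (y-axis) from the most recent birth cohort were plotted against the corresponding 33-quantiles of height (x-axis) from the earliest birth cohort". No centring, standardising or shifted reference line is mentioned here or elsewhere in the SAP.

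Three reading rules follow:

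- **On the line.** For an unchanged distribution, "regardless of overall gains or decreases in height within the country, the QQ plot will fall on the line of equality (line y=x".
- **Above the line.** "If segments of the QQ plot fall above the line, it indicates that certain segments of the population experienced disproportionate gains in height".
- **Below the line.** "if the plot falls below the line of equality, it indicates that segments of the population experienced declines in height across birth cohorts".

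The mean-difference plot, described next, compares the same two cohorts and reads distance from zero as plain gain or loss: "Points that fall below the line at zero indicate losses in height at that place in the distribution".

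The plots have an assigned purpose: "Research Questions 2 and 3 will be addressed using both graphical and statistical approaches". At the end of the Background, question 2 asks whether changes in the mean go with changes in dispersion. Question 3 is to "determine whether patterns exist with regard to which parts of the height distribution experience the greatest height gains or losses across birth cohorts".

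**The concern.** The first rule treats y = x as a line about shape only, to which a country returns whatever happened to its average height. On the raw centimetre scale, y = x means that nothing changed, neither level nor shape. The second rule then calls points above it disproportionate, and a country where all women gained the same amount meets that description.

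The Background sets the study against the hypothesis that dispersion stays roughly constant while the average moves. A uniform gain is that pattern exactly. Followed literally, the rule would report it as its opposite, on a plot meant to help answer questions 2 and 3.

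**Working it through.** The SAP gives no figure for this rule, so there is none to reproduce. The check is algebra, followed by an illustration at the SAP's own 33 quantiles (1st, 4th, …, 97th).

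**Algebra.** Let Q₁(p) and Q₂(p) be the height quantiles of the earliest and most recent cohorts. If the shape is unchanged and the level moves by d, then Q₂(p) = Q₁(p) + d for every p. With x = Q₁(p) and y = Q₂(p), y − x = d at every point. The points lie on y = x + d, which coincides with y = x only when d = 0. This holds for any mean, SD or shape.

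**Illustration.** These inputs are assumptions and are not in the SAP: normal heights, earliest-cohort mean 155 cm and SD 6 cm, recent SD either 6 or 6.6 cm. Then

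y − x = d + (SD₂ − SD₁) × z(p), and slope = SD₂ / SD₁.

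For d = +2 and SD₂ = 6.6:

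- 1st percentile: 2 + 0.6 × (−2.3263) = 0.604 cm
- 97th percentile: 2 + 0.6 × 1.8808 = 3.128 cm
- slope: 6.6 / 6 = 1.10

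| d (cm) | Recent SD | Above / on / below y = x | y − x (cm) | Slope | Largest distance from y = x + d (cm) |
|---|---|---|---|---|---|
| 0 | 6.0 | 0 / 33 / 0 | 0 | 1.00 | 0 |
| +0.5 | 6.0 | 33 / 0 / 0 | 0.5 throughout | 1.00 | 0 |
| +2 | 6.0 | 33 / 0 / 0 | 2.0 throughout | 1.00 | 0 |
| −2 | 6.0 | 0 / 0 / 33 | −2.0 throughout | 1.00 | 0 |
| +2 | 6.6 | 33 / 0 / 0 | 0.604 to 3.128 | 1.10 | 1.396 |
| −2 | 6.6 | 0 / 0 / 33 | −3.396 to −0.872 | 1.10 | 1.396 |
| 0 | 6.6 | 16 / 0 / 17 | −1.396 to 1.128 | 1.10 | 1.396 |

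A skewed simulated sample shifted by 2 cm also gave a difference of 2.0 cm at every quantile.

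**What the table shows.**

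- A uniform +2 cm gain and a +2 cm gain with rising spread both put 33 of 33 points above y = x. The rule gives both the same label, although only the second is disproportionate.
- Distance from y = x adds the shift and the shape change together.
- Distance from y = x + d is zero for every pure shift and is the same, up to 1.396 cm, for the same change in spread whatever the shift. Slope likewise depends only on spread here.

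**The case against.** The strongest defence is that little depends on these sentences. The QQ plot is descriptive, and no test, threshold or count of countries is tied to it. The points themselves are plotted correctly. The mean-difference plot shows a uniform shift as a flat line at d. The SAP also tabulates changes in mean and SD, compares SDs with an F-test, and models SD on the mean and the 5th and 95th percentiles on the median. All of this stands, and it limits the consequence.

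A reader might also infer more than the SAP supports:

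- *Every country whose mean changed would be labelled disproportionate.* Not so. The word is applied only above the line. Below it the SAP speaks of declines, which is true of a uniform loss; such a country is misread only through the first rule, under which leaving y = x implies a changed distribution. Where spread also changed, some disproportion is real.
- *The two kinds of plot contradict each other throughout.* Below their reference lines they agree. They part over the label above the line and over where an unchanged shape should fall.
- *Question 3 cannot be answered from y = x.* It asks where gains or losses are greatest, and comparing distances from y = x across quantiles does answer that.

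One defence fails. Taking an unchanged distribution to mean an identical one does not rescue the first rule, because the same sentence expressly allows the overall level to move. Nor can the quantiles be assumed centred: reading points below the line as declines makes sense only on the raw scale.

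**Conclusion.** The point holds, limited to the reading of the QQ plots. The first rule is mathematically false for any non-zero shift. The second turns a uniform gain into disproportionate gains at all 33 plotted quantiles. The below-the-line rule is correct as a statement about level.

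The algebra needs no assumption about the height distribution; the mean of 155 cm, the SDs and the shifts serve only as illustration. The conclusion takes an unchanged shape to mean an equal shift in centimetres, the sense that matches the constant-dispersion hypothesis in the Background.

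It would go too far to infer that the SAP as a whole cannot separate shift from shape change. Its other analyses can, and none of them relies on this rule. The text should still be corrected before the plots are interpreted, since a written reading rule that is false invites the wrong conclusion on the question the study poses.

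**What to change.** In the QQ-plot paragraph of the SAP:

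1. Delete the clause that exempts overall gains or decreases, and state that y = x means no change in level or shape.
2. Read points above or below y = x simply as gains or losses at that quantile, dropping the word *disproportionate* from that sentence.
3. Add a second reference line, y = x + d, to each country's plot. Fix d as the recent-minus-earliest difference in median height for that country; the median is already the reference measure in the planned percentile models.
4. Define disproportionate change as departure from that parallel line: a slope other than 1, or curvature.

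A matching horizontal line at d on the mean-difference plot would help but is optional, because that plot is already read correctly. The cost is a few sentences and one extra line per QQ plot. No new data are needed, and no other analysis changes.
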